## Abstract

**Background:**

Managing oral anticoagulant treatment (OAT) is a challenge for patients and primary care providers. It requires a high level of patient knowledge and adherence. Studies have shown that insufficient adherence and a low level of patient knowledge about OAT are primary causes for complications. This trial is the first to evaluate the long-term effects of a complex practice nurse-based patient education program in comparison to a patient brochure only.

**Methods and design:**

This trial will be a cluster-randomized controlled trial in 22 general practices (GPs) recruiting 360 patients with OAT. GPs will be randomized into an intervention group or a control group. A baseline questionnaire will assess pre-existing knowledge about OAT. The patients in the intervention group will be educated by a complex education program which consists of a video, a brochure and individual training by a practice nurse. The video gives information about OAT, nutrition, and instructions about how to manage critical situations. The brochure repeats the content of the video. After 4 to 6 weeks, the intervention will be recapitulated. The control group will receive the brochure only. After 6 months, questionnaires will be used in both groups to assess patient knowledge about OAT as well as patients' subjective feelings of safety. Separately, we will evaluate patient records, looking for documented complications and the time spent in the therapeutic range.

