### Patients

In order to minimize sub-sampling bias, all patients with OAT will be identified at the beginning of the trial by searching the GPs' electronic medical records for the laboratory billing code "32015" for INR measurement. The inclusion criteria are age (> 18 years), OAT and willingness to participate in the trial. For dependent patients, both they and their caregivers (e.g. care giving relatives) must be willing to participate. Exclusion criteria include the inability to give informed consent and/or the lack of a caregiver willing to participate in the study. Also, nursing home residents, patients only seen in cross coverage, or patients with an insufficient command of the German language will be excluded. Lastly, patients managing anticoagulation with self-monitoring (PSM) will also be excluded.

During their next visit for INR-measurement age and gender of all eligible patients will be recorded. Patients will receive an information leaflet regarding the purpose and content of the study. Patients willing to participate will fill in a consent form. If there are further questions, patients, caregivers and/or practice nurses are encouraged to contact the study doctors.

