## Randomization

The randomization of the GPs to the intervention or control group will be conducted externally by Department of Medical Statistics, University Medical Centre Göttingen using a computer routine (allocation ratio 1:1).

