## Intervention

Practice nurses will attend a preparatory course, which will enable them to provide individual training sessions for patients based on the content of the video and brochure. The preparatory course for the practice nurses will include simulation (role play).

Patients in the intervention group will be shown an educational video and receive a patient information brochure. The video (20 minutes) provides information about OAT based on up-to-date scientific literature. It addresses common questions about OAT (Table 1). The patient information brochure was designed in accordance with the DISCERN criteria and complements the video [21].

**Table 1 T1:** Content of the video

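### The article does not fix patient consent and baseline testing before a practice learns its arm, so enrolment and the baseline score could depend on allocation

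*Protocol article*

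**What the plan says.** - **Order of steps.** The abstract (Methods and design) is the only place that runs through the steps in sequence: "GPs will be randomized into an intervention group or a control group. A baseline questionnaire will assess pre-existing knowledge about OAT". Education follows.
- **Randomisation.** Under Randomization: "The randomization of the GPs to the intervention or control group will be conducted externally by Department of Medical Statistics", in a 1:1 ratio. No time is given relative to patient consent or baseline testing.
- **Identifying patients.** Under Patients: "all patients with OAT will be identified at the beginning of the trial by searching the GPs' electronic medical records for the laboratory billing code". The stated purpose is to limit sub-sampling bias.
- **Approach and consent.** Under Patients: "During their next visit for INR-measurement age and gender of all eligible patients will be recorded"; then "Patients will receive an information leaflet regarding the purpose and content of the study"; and "Patients willing to participate will fill in a consent form". Further questions from patients, caregivers or practice nurses go to the study doctors.
- **Nurse training.** Under Intervention: "Practice nurses will attend a preparatory course, which will enable them to provide individual training sessions for patients". The course is not dated relative to recruitment.
- **Baseline measurement.** Data collection says that demographic data and knowledge are collected at baseline. It names neither who administers the questionnaire nor its timing relative to randomisation. Data safety and privacy says that consent forms and questionnaires are mailed separately.
- **Use of the baseline score.** Statistical analysis enters baseline knowledge as a fixed effect in the mixed model for the primary outcome, and possibly other factors if the groups are imbalanced.

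**The concern.** In a cluster trial, concealing the assignment of practices does not conceal the arm from the patients and staff who take part in later recruitment. Here each patient consents voluntarily, at a visit whose date varies. The arms ask very different things of patients: a 20-minute video, a 20 to 30 minute session and a recap on one side, a brochure on the other. If the arm is known at that visit, two things can go wrong.

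1. **Selection.** Patients who agree to an educational programme may be more motivated to learn than those who agree to receive a brochure. The primary outcome is the number of correct answers on a 13-item knowledge questionnaire, which motivation can plausibly affect.
2. **A contaminated covariate.** If knowing the arm changes what is said or read before the baseline questionnaire, the baseline score is no longer a measurement untouched by allocation, and adjusting for it can itself introduce bias.

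Neither problem can be fully repaired in the analysis once recruitment is over.

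**Working it through.** **Inputs from Statistical analysis:** 22 practices (11 per arm at 1:1), 15 patients per practice, ICC 0.05, standardised effect 0.41, two-sided 5%, power at least 80%.

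**Step 1: reproduce the stated power (normal approximation).**
- Design effect = 1 + (15 − 1) × 0.05 = 1.70.
- Effective patients per arm = 165 / 1.70 = 97.06.
- SE of the standardised difference = √(2 / 97.06) = 0.1435.
- Power = Φ(0.41 / 0.1435 − 1.96) = 0.815, in line with the stated figure of at least 80%.

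**Step 2: type I error if selection leaves a bias b in the six-month comparison.** The formula is P(Z > 1.96 − b/SE) + P(Z < −1.96 − b/SE). The values of b are assumptions; the documents give none.

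| Assumed b (SD) | Share of 0.41 | Two-sided type I error |
|---|---|---|
| 0 | 0% | 5.0% |
| 0.05 | 12% | 6.4% |
| 0.10 | 24% | 10.7% |
| 0.15 | 37% | 18.1% |
| 0.20 | 49% | 28.6% |

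The bias could also run against the intervention: b = 0.10 SD in that direction lowers power from 81.5% to Φ((0.41 − 0.10) / 0.1435 − 1.96) = 57.9%.

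**Step 3: type I error if knowledge of the arm shifts the baseline score itself.** Suppose the intervention arm's baseline score moves by s SD with no matching change at follow-up, and the baseline to follow-up correlation is ρ (both assumed). Adjustment then moves the estimate by −ρs, and the SE becomes 0.1435 × √(1 − ρ²).
- ρ = 0.3, s = 0.1: shift −0.03 SD, type I error 5.6%.
- ρ = 0.5, s = 0.2: shift −0.10 SD, type I error 12.7%.
- ρ = 0.7, s = 0.3: shift −0.21 SD, type I error 53.5%.

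**Step 4: set each stated safeguard against the gap.**
- External randomisation protects the assignment of practices, not the later enrolment of patients.
- The billing-code search settles who is eligible, not who agrees.
- The age and gender record of all eligible patients can reveal imbalance on two variables, but not on motivation.
- Baseline adjustment helps when selection acts through true baseline knowledge. It does not remove selection on unmeasured motivation, and under step 3 it can add bias.

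**The case against.** The strongest objection is that the sequence is read from two adjacent sentences in an abstract. In the body of the article, Patients comes before Randomization, and the search takes place at the beginning of the trial. That is an order of topics rather than a schedule, but it shows that the abstract cannot settle the matter. Figure 1, the flow chart, is not reproduced here and may show the order. An article also condenses a fuller protocol, which may hold such operational detail.

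This stands as far as it goes. A reader might infer that practices recruit with their arm openly known, that they administer the baseline test themselves, or that nurses issue different invitations by arm. The documents support none of these. They are silent on masking, name no administrator, say that questionnaires are mailed, and describe a single leaflet. Nor do they say which practices' nurses attend the course. Its place under Intervention suggests the intervention practices, in which case attendance would reveal the arm.

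It is also fair that the safeguards are real, that the bias sizes are assumed, and that no figure in the protocol is wrong on this point.

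What the objection does not supply is any statement that allocation is held back. The order of randomisation, consent and baseline is a core feature of a cluster design rather than an analysis detail, and the one sequential account puts randomisation first.

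**Conclusion.** The point holds in a limited form. The article lists randomisation before the baseline questionnaire and nowhere requires consent and baseline testing to precede disclosure of the arm or nurse training. A practice could follow the text exactly and still enrol patients with the arm known. The stated safeguards reduce or expose the resulting bias without removing it.

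The size is conditional: about 6% to 29% type I error for an assumed residual bias of 0.05 to 0.20 SD, using the unadjusted SE and a normal approximation. These figures show how sensitive the trial would be to such a bias, not how likely the bias is. A reader might go further and conclude that the knowledge comparison is biased as designed; the documents do not support that, because they describe neither open recruitment nor any difference in enrolment. The point is a cheap improvement to the design.

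**What to change.** State the sequence in Patients, Randomization and Data collection, and make Intervention and the abstract agree with it:

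1. In each practice, complete the billing-code search and fix the list of eligible patients.
2. Obtain consent and the completed baseline questionnaire from those patients.
3. Only then does the statistics department release that practice's allocation, and only then do its nurses attend the preparatory course.
4. Report eligible and consented counts by arm, with the age and gender of both groups. Age and gender are already to be recorded.
5. If any patient is enrolled after release, keep that patient in the primary analysis and add a sensitivity analysis restricted to patients consented before release. Making the restricted set primary would discard enrolled patients and reduce power.

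If this order is already intended, a sentence saying so is enough.

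The cost is a few weeks between recruitment and training in each practice, and the scheduling of the nurse course around it. The targets of 330 analysed and 360 recruited patients, and the power of 0.815, are unchanged.

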**Discussion:**

This trial will start in January 2011. This trial will evaluate the long-term effectiveness of a video-assisted education program on patients with OAT in comparison to a patient information brochure. Most previous studies have evaluated knowledge directly after an educational intervention. Our trial will look for long-term differences in basic knowledge of OAT. We expect that our complex patient education program effectively increases long-term basic knowledge about OAT. Although the population of our study is too small to observe differences in adverse effects, we expect to discover differences in secondary outcomes, such as the time spent in the therapeutic range.

**Trial registration:**

Deutsches Register Klinischer Studien (German Clinical Trials Register): DRKS00000586

Universal Trial Number (UTN U1111-1118-3464)

## Background

Managing oral anticoagulant treatment (OAT) is a challenge for patients in their daily life. In Germany, more than a half million patients are taking phenprocoumon daily and this number will increase in the next few years due to the demographic development, as in other industrialized countries. The incidence and prevalence of atrial fibrillation (AF), the major indication for oral anticoagulation, increases progressively with age, and approximately 50% of patients with AF are 75 years or older. With the aging of population, the number of adults with AF and OAT will increase markedly over the next several decades [1]. Intra- and inter-individual variability of the dose-effect relationship is affected by several factors such as patient adherence, nutritional patterns, genetic differences and drug interactions [2-4]. Serious complications arise from insufficient or excessive anticoagulation. Main complications of OAT are bleeding complications, which occur in 0.3 to 0.4% of all patients with OAT every year [5]. Unlike in many other countries, in Germany phenprocoumon is the most commonly-used drug for OAT. An accurate estimation of the complication rate in association with phenprocoumon does not exist. An English study assessed an annual bleeding risk of 9.0% for Warfarin which is usually prescribed in USA and the United Kingdom [6].

Lack of patient education, misjudgements of the indication, incorrect and misleading documentation, insufficient communication and cooperation as well as lack of patient's integration into the therapy are common causes for an unsatisfactory management of OAT [7]. Studies have confirmed that insufficient adherence and a low level of patient knowledge about OAT are the primary causes for complications [7-9]. Therefore, it is necessary to increase patient knowledge. Patient self-management (PSM) of international normalized ratio (INR) shows that intensive obligatory training lowers the risk for severe bleeding complications [10-12]. A systematic review concluded that PSM is not feasible for many patients because of patients' inability to complete training [13,14]. Another barrier for implementation of PSM is costs [15]. A standardized education program in primary care for patients who are not suitable for PSM is lacking in many countries [7,9]. The best strategy for educating patients about oral anticoagulation has not been determined yet [16]. In Germany, general practitioners manage patients with OAT. Some general practitioners use self-written patient information brochures to inform patients about OAT. However, the contents and quality of these brochures can differ greatly and sometimes even contradict evidence from published literature.

So far, an Italian study has evaluated the short-term effects of an education program which was well accepted by the patients but did not improve the time spent in the therapeutic range in the short term [17]. In contrast, a French study could show that an education program lowers the complication rate of patients without PSM [18]. An Italian study assessed the acceptance of an educational program for patients with OAT but not its effectiveness [19].

Based on these studies, our trial is the first to evaluate the long-term effects of a complex practice nurse-based patient education program in comparison to a patient brochure only.

## Hypothesis

A practice nurse-based, individual and video-assisted patient education program effectively increases long-term basic knowledge about OAT. Patients participating in this complex education program will spend more time in the therapeutic range and will have fewer complications in comparison to the control group.

## Aim

The aim of this trial is to evaluate the long-term effects of a complex patient education program about OAT in comparison to a patient information brochure only.

## Objectives

▪ To investigate long-term effectiveness (6 months) of a complex patient education program about OAT on patient knowledge

▪ To assess the effect of a complex patient education program about OAT on time spent in therapeutic range

▪ To investigate long-term effectiveness (6 months) of a complex patient education program about OAT on subjective feeling of safety

▪ To assess effect of a complex patient education program about OAT on complications related to OAT

## Method

This trial will be a cluster-randomized controlled educational trial consisting of 22 general practices (GPs) which are expected to recruit 360 patients with OAT. Practices will be randomized into an intervention group or a control group (Figure 1).

**Figure 1 F1:**
[figure not shown]
**Flow-chart**. The flow-chart gives an overview about the trial.

We obtained a Universal Trial Number (UTN: U1111-1118-3464) and registered this trial in the German Clinical Trials Registry (DRKS00000586).

## Patient recruitment

### General practitioners

Monitoring and dose adjustment for OAT is managed by general practitioners in Germany. GPs in central Germany (Göttingen, Braunschweig and the surrounding areas) will be invited to participate in the trial by mail. Addresses have been obtained from the local health boards. In case of non-response to the letter, GPs will be contacted by telephone or personally. From previous experience, it seems likely that roughly 15 - 20% will agree to participate [20].

### Patients

In order to minimize sub-sampling bias, all patients with OAT will be identified at the beginning of the trial by searching the GPs' electronic medical records for the laboratory billing code "32015" for INR measurement. The inclusion criteria are age (> 18 years), OAT and willingness to participate in the trial. For dependent patients, both they and their caregivers (e.g. care giving relatives) must be willing to participate. Exclusion criteria include the inability to give informed consent and/or the lack of a caregiver willing to participate in the study. Also, nursing home residents, patients only seen in cross coverage, or patients with an insufficient command of the German language will be excluded. Lastly, patients managing anticoagulation with self-monitoring (PSM) will also be excluded.

During their next visit for INR-measurement age and gender of all eligible patients will be recorded. Patients will receive an information leaflet regarding the purpose and content of the study. Patients willing to participate will fill in a consent form. If there are further questions, patients, caregivers and/or practice nurses are encouraged to contact the study doctors.

## Randomization

The randomization of the GPs to the intervention or control group will be conducted externally by Department of Medical Statistics, University Medical Centre Göttingen using a computer routine (allocation ratio 1:1).

## Primary outcome

The primary outcome is the number of correctly answered questions from the 13-item OAT-questionnaire.

## Secondary outcome

Secondary outcomes are time spent in therapeutic range, subjective feeling of safety and complications related to OAT.

## Intervention

Practice nurses will attend a preparatory course, which will enable them to provide individual training sessions for patients based on the content of the video and brochure. The preparatory course for the practice nurses will include simulation (role play).

Patients in the intervention group will be shown an educational video and receive a patient information brochure. The video (20 minutes) provides information about OAT based on up-to-date scientific literature. It addresses common questions about OAT (Table 1). The patient information brochure was designed in accordance with the DISCERN criteria and complements the video [21].

**Table 1 T1:** Content of the video

**1. Introduction**
- aim of this video
- scene: a patient newly on oral anticoagulant therapy consults her GP and has questions
**2. General information about oral anticoagulation**
- Why do I have to take oral anticoagulants?
- active agent: Phenprocoumon
- Explanation of stroke
- How long do I have to take oral anticoagulants?
- How do I notice that my coagulation not sufficiently inhibited?
**3. Nutrition**
- Do I have to follow a special diet?
- Which food contains a high amount of vitamin K (usual consumption quantity)?
- Alcohol, coffee
- Nutrition on holidays
**4. Drug-interactions & influences on OAT**
- Drug interactions, influence of non-prescription drugs (herbal drugs)
- Discontinuation or prescription of a new drugs
- Which non-prescription pain-killer is the safest in combination with oral anticoagulant therapy?
**5. Adherence**
- Monitoring
- Coagulation test, meaning of Quick- and INR-level, therapeutic range
- What should I do if I forgot a dosage?
- Recognition of critical situations and how to react (e.g. bleeding, black stool)
- In which situations should I mention that I receive oral anticoagulants? (e.g. pharmacy, dentist, injections)
**6. Summary of the main points**

Practice nurses will use the brochure as a guide to discuss knowledge gaps about OAT after the video in an individual training session lasting about 20-30 minutes. The intervention group has the option of another individual training if necessary. After 4 to 6 weeks when the next blood work is done, patients will be asked to fill in a short knowledge assessment questionnaire, designed to recap what was learned in the video and individual training session.

## Control

The control group will only receive the patient information brochure.

## Data collection

Demographic data and knowledge about OAT will be collected at baseline (Additional file 1). After six months, knowledge about OAT and the subjective feeling of safety in both groups will be assessed (Figure 1). The self-developed questionnaire is based on the content of the video and the information brochure. The questionnaire was piloted with 12 patients previously and optimized accordingly.

At the end of the trial after 6 months we will collect data about complications related to OAT and the INR results from patient records in both groups.

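### No baseline is listed for feeling of safety and no pre-enrolment INR window is specified for time in therapeutic range, which costs precision in two secondary outcomes

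*Protocol article*

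**What the plan says.** All references are to the protocol article.

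- **Baseline content.** Data collection states: "Demographic data and knowledge about OAT will be collected at baseline". The abstract (Methods and design) agrees: "A baseline questionnaire will assess pre-existing knowledge about OAT".
- **Feeling of safety.** Data collection places it at follow-up: "After six months, knowledge about OAT and the subjective feeling of safety in both groups will be assessed". The abstract also names it only at 6 months.
- **INR data.** Data collection says: "At the end of the trial after 6 months we will collect data about complications related to OAT and the INR results from patient records". This fixes when and from where the values are taken, but not which calendar period they cover. Statistical analysis names Rosendaal's method for TTR and gives no period either.
- **Baseline adjustment.** Statistical analysis describes a mixed linear model with baseline knowledge as a fixed effect and practice as a random effect, for the primary endpoint only. No model is described for any secondary outcome.
- **Weight given to TTR.** It appears in the Hypothesis and the Objectives. The abstract's Discussion adds: "we expect to discover differences in secondary outcomes, such as the time spent in the therapeutic range".

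**The concern.** The plan measures its primary outcome before and after and adjusts for the earlier value. It would also add factors to that model if the arms turn out unbalanced. For feeling of safety and TTR, the text provides no earlier value to inspect or adjust for. With only 11 practices per arm, a sizeable chance difference between arms is not rare, and it could be neither shown nor removed.

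The two outcomes differ in how far this can be repaired. If the safety items are not asked before the intervention, no later analysis plan can recover them. For TTR, the earlier INR values should usually be on file, because patients are identified through the billing code for INR measurement (section Patients). A window fixed before extraction is enough.

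At stake is precision in two of the three secondary outcomes, one of which the authors expect to show a difference.

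**Working it through.** **Inputs from the article.** 22 practices (Statistical analysis), allocated 1:1 (Randomization), so k = 11 per arm; m = 15 patients per practice; ICC = 0.05; two-sided 5%; power at least 80% at a standardised effect of 0.41.

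**Assumed, because the article gives no values.** The ICC of 0.05 also applies to feeling of safety and TTR. The correlation r between baseline and follow-up is 0.3 to 0.5, equal at patient and practice level.

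**1. The plan's own figure.**
- Design effect = 1 + (15 − 1) × 0.05 = 1.70.
- Effective n per arm = 165 / 1.70 = 97.06.
- Power at 0.41 SD, normal approximation = 81.5%.

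The stated power of at least 80% reproduces on this basis.

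**2. Unadjusted precision for a continuous secondary outcome.**
- SE = √(2 × 1.70 / 165) = 0.1435 SD.
- Detectable effect at 80% power, normal: (1.960 + 0.842) × 0.1435 = 0.40 SD.
- Detectable effect, t on 20 df: (2.086 + 0.860) × 0.1435 = 0.42 SD.

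**3. Chance difference between arms before any intervention.** Its standard deviation is the same 0.1435.
- P(|difference| > 0.2 SD) = 2 × P(Z > 0.2 / 0.1435) = 16%.
- For an ICC of 0.01 the standard deviation is 0.118 and the probability 9%. For an ICC of 0.10 they are 0.171 and 24%.
- Share of this variance due to practices at ICC 0.05: 15 × 0.05 / 1.70 = 44%.

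The 16% restates the standard error in another form. It is not a second loss on top of it.

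**4. Gain from baseline adjustment.** SE_adj = SE × √(1 − r²). The equivalent multiple of practices is 1 / (1 − r²).

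| r (assumed) | SE (SD) | Reduction in SE | Detectable, normal | Detectable, t (20 df) | Equivalent practices |
|---|---|---|---|---|---|
| none | 0.143 | – | 0.40 | 0.42 | 1.00 |
| 0.3 | 0.137 | 5% | 0.38 | 0.40 | 1.10 |
| 0.5 | 0.124 | 13% | 0.35 | 0.37 | 1.33 |

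**5. The gain in TTR points.** The article gives no SD for TTR. If it were 20 to 25 percentage points (assumed), the detectable difference (normal) would fall by between 0.0185 × 20 ≈ 0.4 points (r = 0.3) and 0.0539 × 25 ≈ 1.3 points (r = 0.5). Patients newly on OAT have no history, so the real gain for TTR would be somewhat smaller.

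**The case against.** **The TTR part rests on silence.** A reader might infer that TTR will not be measured before the intervention. The text does not support that: it dates the extraction, not the period extracted. Because extraction is retrospective, pre-enrolment values are neither planned nor excluded. A condensed article can leave the window and the covariates of a secondary analysis to the full protocol or the SAP. This stands, and the TTR part is limited to recommending that the window be fixed.

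**Randomisation already protects the comparison.** A reader might infer that follow-up-only measurement confounds the programme with existing practice differences. It does not. Practices are allocated 1:1 by an external department, so chance imbalance causes no bias in expectation, and an interval that accounts for clustering covers it. This stands in full.

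**The gain is modest.** A reader might also infer that only a large TTR difference is detectable without adjustment. Statistical analysis itself calls 0.41 a medium effect, and 0.40 to 0.42 SD is about the same size. Adjustment lowers the threshold to 0.35 to 0.40 SD, which is useful but not decisive. This stands too.

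**The baseline instrument is not shown.** Additional file 1 and Figure 1 are not available, and the questionnaire might contain safety items. That is possible, but both descriptions of the baseline omit them, and both place feeling of safety at 6 months.

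None of this removes the feeling-of-safety point. What is collected at baseline is a data-collection decision that the article states, and an unasked item cannot be restored later.

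**Conclusion.** The point holds as a cheap improvement to two secondary outcomes, not as an error. For feeling of safety, the stated baseline leaves it out. For TTR, no pre-enrolment window or baseline-adjusted analysis is specified, although the planned extraction would allow one.

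Both comparisons remain valid, and the primary outcome, which has a baseline and is adjusted for it, is untouched. What is lost is a 5% to 13% reduction in the standard error, worth 10% to 33% more practices, together with the ability to show that the arms were comparable or to adjust where they were not.

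These figures rest on an assumed correlation of 0.3 to 0.5 and on an ICC that the article gives for its sample-size calculation, not for these outcomes. The direction does not depend on those values as long as baseline and follow-up are correlated. The size does.

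**What to change.** 1. Add the feeling-of-safety items to the existing baseline questionnaire. This must happen before enrolment starts.
2. At the record extraction already planned, also take INR values from a pre-specified window before enrolment, for example 6 months, and compute baseline TTR by the same Rosendaal method as at follow-up.
3. Analyse each of the two outcomes in a mixed model with a random practice effect and its own baseline as a covariate. For TTR, include an indicator for patients newly on OAT who have no history, so that they stay in the analysis.

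**Cost.** A few more questionnaire items, slightly more abstraction time, and consent wording that covers the earlier INR values. New starters will still have no baseline TTR. No extra visit and no change to the sample size is needed.
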